**Methods/Materials:**

A double-blind randomized clinical trial (RCT) has been designed. All participants will be randomized from a pre-set sequence. The intervention design has been elaborated from the CONSORT guidelines. This study has been registered at Clinicaltrial.gov (NCT06272539). Sample size was calculated using G Power® Sample size software (University of Düsseldorf). The calculation was based on a moderate effect size of 0.7 (partial η2 = 0.70, α = .05, power = 0.95), resulting in a total of 40 patients. Assuming a 30% dropout rate, 52 participants will be recruited in total. Two sessions per week will be scheduled for 8 weeks with a total of 16 sessions. Each work session will have a duration of 60 minutes. The exercise will be adapted according to the phases based on the results already published, limiting in each phase the degrees of flexion and extension of the spine to avoid the risk of electrode migration. Primary outcomes will be functionality, satisfaction, strength, psychosocial variables, quality of life and pain perception.

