**Fig 1 pone.0309935.g001:**
[figure not shown]
Execution schedule–recruitment, intervention, and reassessment.

This study will be a research protocol for two groups: SCS and core and control motor exercises with an allocation ratio of 1:1. Data will be collected from April 2024 to January 2026. All participants will sign an informed consent form, prepared in accordance with the ethical guidelines of the Helsinki Declaration [29]. The study protocol was approved by the Ethics Committee on January 24, 2024 (ID: 2023 10 1435). This study was prospectively registered in the Clinical Trials (Registration number: NCT06272539) (Supplementary file 1)

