## 4. Sample size

The sample size will be estimated using GPower® software (Franz Faul, Universität Kiel, Kiel, Germany), version 3.1.9.2. As there are no similar studies allowing for the calculation of sample size based on reference means and standard deviations, a comparison will be made using the difference between two dependent means of 1.95 normal populations, assuming equal standard deviations of 3,2 according to the results obtained from a prior study [37]. Thus, the calculation will be based on the primary outcome of "Disability" and will consider an effect size of 0.70, a power of 0.95 for ANOVA repeated measures, and an alpha error of 0.05. A total of 40 participants (20 subjects per group) will be included in this study. Moreover, considering the probability of loss during follow-up (30%), 12 more participants considering dropout (6 participants per group) will be included, resulting in a total of 52 participants. The possibility of increasing the number of subjects will be explored in case of insufficient statistical power to reach these predefined levels. In the event of dropouts, noncompliance, or absence of results, an intention-to-treat analysis will be conducted.

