#### 8.2.2 Analysis of the outcome measures

Following the Consolidated Standards of Reporting Trials (CONSORT) guidelines on the reporting of RCTs, a per-protocol analysis will be performed. The normality assumption will be checked with the Kolmogorov–Smirnov test and box-plot analysis, while the homogeneity of the variance will be tested through the Levene test. To analyze the acute and short-term effects of SCS and SCS combined with core and control motor exercise on PSPS T2, a two-way ANOVA for repeated measures with experimental groups (i.e., Post3weeks, Post2months, Post6months) as factors will be used, followed by Tukey corrections, to examine time, group, and interaction effects through within- and between-group comparisons (primary and secondary outcomes). The results will be presented as the mean difference (MD) and confidence interval at 95% (IC95%). Effect size (ES) will be estimated by calculating Cohen’s d coefficient. All analyses will be performed using the statistical analysis software SPSS 24 (IBM Inc., Chicago, Illinois, USA). In the case of dropouts during the study or if the statistical power is less than the established 80%, an intention-to-treat principle analysis will be performed [71]. The normality of the data will be tested by visual inspection of histograms, and the characteristics of the participants will be presented using descriptive statistical tests. To assess between-group differences in response to treatment at each post-baseline time point, the mean between-group differences and their associated 95% confidence intervals (CI) will be calculated by constructing mixed linear models using interaction terms (group vs. time). The treatment effects will be adjusted by including baseline outcome values as covariates in the model. Statistical analysis will be conducted by a researcher who is not involved in any of the phases of data collection and will receive data in coded form. Minimal clinically important differences are patient-derived scores that reflect changes in a clinical intervention that are meaningful to the patient. To do this from the delta percentage (Δ%) will calculate using the standard formula: change (%) = [(post-test score − pre-test score)/pre-test score] × 100.

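### The dropout allowance is miscalculated: 52 recruited with 30% loss leaves about 36 completers, not the 40 required

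*Protocol article*

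**What the plan says.** Section 4 (Sample size) of the protocol article names disability as the outcome on which the calculation rests and gives its inputs: it "will consider an effect size of 0.70, a power of 0.95 for ANOVA repeated measures, and an alpha error of 0.05". It arrives at a base number: "A total of 40 participants (20 subjects per group) will be included in this study". It then adds the allowance for loss: "considering the probability of loss during follow-up (30%), 12 more participants considering dropout (6 participants per group) will be included". The sum is given as 52. The abstract (Methods/Materials) gives the same total and attaches the rate to recruitment: "Assuming a 30% dropout rate, 52 participants will be recruited in total". Section 2.1 describes two groups "with an allocation ratio of 1:1", so 52 means 26 per group.

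Two other statements bear on how losses count. Section 8.2.2 says that "a per-protocol analysis will be performed", with intention-to-treat brought in if there are dropouts or power is low. Section 4 also mentions intention-to-treat for dropouts, and says that a larger sample may be looked into if power proves insufficient.

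**The concern.** An allowance for dropout exists so that the required number remains after the expected losses. Here the 30% was applied to the wrong base: it was taken of the number wanted at the end and added on, whereas losses occur among those recruited. The three figures (40 required, 30% lost, 52 recruited) therefore cannot all be true together.

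At stake is a headline recruitment figure, printed in two places, that misses the plan's own target under the plan's own assumption. The analysis named first is per-protocol, in which patients who are lost drop out of the data, so the number remaining matters.

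**Working it through.** **Inputs, all from the protocol article**
- Required number: 40, 20 per group (section 4).
- Loss: 30% (section 4 and abstract).
- Extra patients: 12, 6 per group (section 4).
- Recruited: 52 (section 4 and abstract), 26 per group at 1:1 (section 2.1).

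**Step 1. Reproduce the plan's figure.** Required × (1 + loss) = 40 × 1.30 = 52; per group, 20 × 1.30 = 26. The printed total is matched exactly.

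**Step 2. Apply the loss to those recruited.** Recruited × (1 − loss) = 52 × 0.70 = 36.4, about 36; per group, 26 × 0.70 = 18.2, about 18. The shortfall is 40 − 36 = 4, and 4/40 = 10%.

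**Step 3. Loss that 52 can absorb.** 12/52 = 23.1%.

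**Step 4. Number needed for 40 completers at 30% loss.** Required/(1 − loss) = 40/0.70 = 57.1; per group, 20/0.70 = 28.6, so 29. The total is 58, six more than 52. Check: 58 × 0.70 = 40.6.

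**Step 5. Does this depend on the base of 40?** No. Multiplying by 1.30 and then losing 30% always keeps 1.30 × 0.70 = 0.91 of the target, before rounding to whole patients.

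**Step 6. What 36 in place of 40 does to power.** The plan does not say clearly which calculation gave 40. Section 4 speaks of a "difference between two dependent means of 1.95 normal populations, assuming equal standard deviations of 3,2" (1.95/3.2 = 0.61), then of an effect size of 0.70 for repeated-measures ANOVA; the abstract gives 0.70 as a partial η². I could not reproduce 40 from any of these, so the table shows a range. All rows use alpha 0.05, and the t-tests are two-sided. The ANOVA rows assume a correlation of 0.5 between measurements and 2 to 6 measurements; neither figure is stated for the calculation. For two groups, d = 0.70 corresponds to f = 0.70/2 = 0.35, and partial η² = 0.70 corresponds to f = √(0.70/0.30) = 1.53.

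| Calculation | Power at 40 | Power at 36 | Loss (points) |
|---|---|---|---|
| Two-sample t-test, unadjusted, d = 0.70 | 0.578 | 0.532 | 4.6 |
| Two-sample t-test, unadjusted, d = 0.61 | 0.467 | 0.427 | 4.0 |
| Paired t-test, d = 0.61 | 0.964 | 0.945 | 1.9 |
| Repeated-measures ANOVA, between groups, f = 0.35 | 0.702 to 0.806 | 0.654 to 0.762 | 4.4 to 4.8 |
| Repeated-measures ANOVA, interaction, f = 0.35 | 0.991 to 1.000 | 0.983 to 1.000 | 0 to 0.8 |
| Repeated-measures ANOVA, between groups, f = 0.70 | 0.999 to 1.000 | 0.997 to 1.000 | 0 to 0.2 |
| Repeated-measures ANOVA, between groups or interaction, f = 1.53 | 1.000 | 1.000 | 0 |

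The loss runs from about 0 to 5 percentage points.

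**The case against.** **The 30% might be meant as a share of the 40.** The abstract calls it a dropout rate and puts it beside the number recruited; section 4 calls it a probability of loss during follow-up. Both describe enrolled patients. If 12 losses among 52 were meant, the rate to print is 23%. The text needs correcting either way.

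**Intention-to-treat, or the option of a larger sample, might cover it.** Neither does. Intention-to-treat does not supply outcomes that were never measured, and section 8.2.2 names per-protocol first. Looking into more subjects if power is short is not a dropout allowance, and it leaves the printed sum as it is.

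**About 36 applies only at the end of follow-up.** This stands in part. Visits run to 18 months (section 2.5), while the ANOVA in section 8.2.2 lists the visits at 3 weeks, 2 months and 6 months. The timing of loss is not given, so more than 36 patients may be available at those visits. The mixed model, also in section 8.2.2, can use the data of patients who leave later. Both soften the effect on the results, but neither makes the stated allowance correct.

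**The consequence for power may be small.** This stands. A reader might infer that the error pushes the trial further below its stated 95% power, for instance from 58% to 53%. The documents do not support that. Those figures belong to an unadjusted two-sample t-test, which the plan does not name: section 4 sizes for repeated-measures ANOVA, and section 8.2.2 adjusts for baseline in a mixed model. Under several readings in the table, power stays above 95% with 36. Whether 40 was adequate to begin with is a separate question.

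**Conclusion.** The point holds as an error of arithmetic. Under the plan's own 30% loss, 52 recruited gives about 36 completers (18 per group) against a requirement of 40 (20 per group); 52 tolerates 23% loss; and 40 completers at 30% loss needs 58. This rests only on reading the 30% as a share of those recruited, which is how the abstract presents it.

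The error is modest and should be corrected, but it does not by itself put the trial's conclusions at risk. The power cost of about 0 to 5 points rests on the assumptions listed with the table, and it cannot be narrowed until the base calculation is identified.

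**What to change.** Keep 52 and correct section 4 and the abstract in one of two ways:
- State that, with 52 recruited and 30% loss, about 36 (18 per group) are expected to complete, and give the power for 36. This requires naming the base calculation first: test, effect size and its scale, number of measurements, and correlation.
- State that 52 allows for a loss of about 23%.

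Print 58 (29 per group) only if the sponsor wants 40 completers at 30% loss.

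Either restatement costs one sentence in each place and a less favourable figure; the first also needs the power calculation to be redone. No procedure or analysis changes. The 58 option costs more: six further implanted patients at a single pain unit, and a total that does not fill the blocks of 4 or 8 in section 3 (58 = 14 × 4 + 2, whereas 52 = 13 × 4). If the base of 40 is revised for other reasons, the allowance should be recomputed from the new base by dividing by 0.70.

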### 4.1 Interventions

Patients included in the study will be randomised to receive:

#### 4.1.1 Lumbo-pelvic core stability training program combined with motor control exercises

The experimental group will undertake a lumbo-pelvic core stability training program that incorporates motor control exercises through specific therapeutic interventions at the lumbopelvic center, along with neurostimulation treatment. This intervention plan was designed in accordance with the principles established by Falla et al. [22]. The exercises in each phase are specifically designed to limit the degree of flexion/extension and lumbar traction. Two weekly sessions, each lasting 60 minutes and spanning eight weeks, will constitute a total of 24 sessions. A certified physiotherapist with at least 10 years of clinical experience will administer this treatment.

*Phase 1 (muscular activation)*

In the initial phase of the study, all participants will be instructed on how to engage their abdominal muscles effectively. Feedback and ultrasound imaging will be utilized to ensure proper training of the participants. This phase will last for 15 days, comprising of four sessions, with the primary objective of achieving voluntary neuromuscular control. There is no need for flexion-extension movements in the spine exceeding 65 degrees in both directions during this phase, thus eliminating the risk of electrode migration. Participants will learn to engage their abdominal muscles through techniques such as rib breathing and forced exhalation, which will result in the contraction of the internal obliques, the activation of the multifidus lumbar, and the easing of the abdominal transverse.

The exercises that will be performed during this phase are detailed in Tables 1 and 2.

**Table 1 pone.0309935.t001:** Phase 1 exercise schedule for the first and third sessions.

	Sessions 1 and 3						
	Exercise	Series	Repetitions	Intensity	Duration	Break	Effort
**Block 1**	*Breathing dissociation*	4	15–20	2/10	-	30”	Minimal
	*Iso hip adduction + breathing dissociation*	4	10–12	3/10	-	30”	Minimal
	*Iso horizontal push + breathing dissociation*	4	6–8	6/10	-	30”	Low
**Block 2**	*Hollowing + FB ultrasound*	3	5	4/10	-	30”	Low
	*Iso pelvic retroversion + FB stabilizer + hollowing*	3	12–15	4/10	-	30”	Low
	*Bracing + FB ultrasound*	3	5	7-8/10	-	30”	Moderate
**Block 3**	*Hip abduction in dead bug position with feet against the wall*	4	20–25	9/10	1,3,3	-	High
	*Internal rotation and hip rotation from dead bug position + forced exhalation*	4	5x5”	9/10	-	-	High
	*Iso holds anti extensor facing up*	4	5x5”	7/10	-	120”	Moderate

**Table 2 pone.0309935.t002:** Phase 1 exercise schedule for the second and fourth sessions.

	Sessions 2 and 4						
	Exercise	Series	Repetitions	Intensity	Duration	Break	Effort
**Block 1**	*Hollowing + FB ultrasound*	3	5	4-5/10	-	30”	Low
	*Iso pelvic retroversion + FB stabilizer + hollowing*	3	12–15	4/10	-	30”	Low
	*Bracing + FB ultrasound*	3	5	7-8/10	-	30”	Moderate
**Block 2**	*Iso hip extension push from 90° flexion standing*	4	5x5”	9/10	-	-	Low
	*Bracing + press pallof sitting horizontal with asymmetric feet*	4	8–10	5/10	1,3,2	30”	Low
	*Bracing + press pallof a stride*	4	8–10	5/10	1,3,2	30”	Moderate
**Block 3**	*Monsters walk for medial gluteus guided in parallel*	4	15/side	8/10	1,3,3	30”	Moderate
	*Isotonic clamshell*	4	15–25	9/10	-	-	High
	*Iso holds against rotation facing up in crossed position with hip at 90° and external knees unbalancing + bracing*	4	5x5”	8/10	-	60”	Moderate

*Phase 2A Posture/ alignment*

The second phase of treatment will span from day 16 to day 37 after the intervention. This phase aims to focus on exercises that target the deep spinous-transverse muscles (multifidus), which serve as essential stabilizers for individual spinal segments. As patients have already improved their neuromuscular control during phase 1, the emphasis shifts towards initiating muscle recovery. In this phase, exercises will involve a greater flexion range starting from 65 degrees, similar to phase 1, while the extension range will be extended to 85 degrees. The extension movement of the spine is considered safe as it does not increase neural tension, utilizing the posterior pillar of the facet joints instead. During the 21-day treatment period, patients will attend six monitoring sessions and perform exercises at home safely, following the instructions provided. The exercise progression will be tailored to each patient’s ability based on their pain level. Exercises will be performed from series 1 to 3, with 8 to 15 repetitions, and isometric contractions lasting between 5 and 10 seconds. Breaks between series will last 30 seconds, while breaks between exercises will be 2 to 3 minutes [38].

The exercises for this phase are listed in Tables 3–5.

**Table 3 pone.0309935.t003:** Phase 2A exercise schedule for the first, third and fifth sessions.

	Sessions 1, 3 and 5						
	Exercises	Series	Repetitions	Intensity	Duration	Break	Effort
**Block 1**	*Bracing + FB ultrasound*	3	10	7-8/10	-	30”	Low
	*Iso holds anti extensor facing up*	3	8x5”	7/10	-	30”	Low
	*Iso hold autorotation facing up*, *in cross position with hip at 90° and external knees unbalancing+ bracing*	3	10x5”	8/10	-	30”	Moderate
**Block 2**	*Ascendant row for dorsal external extension a stride with blocked lumbar*	3	12–15	8/10	1,3,3	-	Moderate
	*Dorsal inclination with iso push from knight position (closed side) + exhalation*	3	5x5”	8-9/10	-	-	Moderate
	*Iso push hip extension standing in one leg over asymmetric ground + soft hinge with KB in goblet squat*	3	10	7/10	-	120”	Low
**Block 3**	*Isotonic clamshell*	4	15–25	9/10	-	-	High
	*Bracing + vertical press pallof a stride*	4	8–10	5/10	1,3,2	-	Low
	*Monsters walk for medial gluteus guided in parallel*	4	15/side	9/10	1,3,3	120”	High

**Table 4 pone.0309935.t004:** Phase 2A exercise schedule for the second, fourth and sixth sessions.

	Sessions 2, 4 and 6						
	Exercise	Series	Repetitions	Intensity	Duration	Break	Effort
**Block 1**	*Dead bug with support + iso holds from anti extension arms + bracing*	3	6x5”	8/10	-	30”	Moderate
	*Dead bug with switch changing support + iso hold antiextension arms + bracing*	3	10	8/10	-	30”	Moderate
	*Iso hold antirotation facing up*, *cross position with hip at 90° and external instability from knees + bracing*	3	10x5”	8/10	-	30”	Moderate
**Block 2**	*Press pallof horizontal standing over asymmetric ground + bracing*	3	12–15	8/10	1,3,3	-	Moderate
	*Iso push hip extension at 30°*, *standing up with blocked core*	3	5x5”	8-9/10	-	30”	Moderate
	*Standing in one leg iso push over asymmetric ground + soft hinge in goblet squat*	3	10	7/10	-	120”	Low
**Block 3**	*Hip abduction in stable sitting*, *iso push creating speed peaks and contraction intensity*	4	5x7”	9/10	-	30”	High
	*Vertical press pallof sitting with asymmetric legs from 130° arms flexion*	4	8	7/10	-	30”	Low
	*A stride iso push in extension from arms and from below creating spinal extensor activation + creating speed peaks and intensity contraction*	4	10x7”	8/10	-	60”	Moderate

**Table 5 pone.0309935.t005:** Phase 2A home exercises schedule.

	Home exercises						
	Exercise	Series	Repetitions	Intensity	Duration	Break	Effort
**Block 1**	*Clamshell with blocked lumbar*	3	20–25	8/10	-	-	Moderate
	*Iso push hip extension at 30°*, *standing with blocked core*	3	5x7”	9/10	-	-	High
	*Step with pre-iso push to 3” step*	3	6–8	7/10	-	120”	Low
**Block 2**	*Monsters walk for medial gluteus guided in parallel*	3	15/side	8/10	-	-	Moderate
	*Standing Iso hold anti extensor*	3	8x5”	7/10	-	30”	Low
	*Standing press pallof horizontal over asymmetric ground + bracing*	3	12–15	8/10	1,3,3	-	Moderate

Exercises for this phase are shown in Tables 3–5.

*Phase 2B Posture/alignment*

Phase 2B will comprise between day 38 and day 60 after the intervention. It will follow the same objectives and attributes as phase 2, with the additional instruction of voluntary spine traction movement to enhance posture control. All other aspects will remain unchanged.

*Phase 2C Posture/alignment*

Phase 2C encompassed the period from days 61 to 90 following the intervention. During this phase, the range of motion was increased from 90 degrees of flexion to 85 degrees of extension. To ensure proper exercise adherence, all exercises were performed isometrically. The progression of exercises was customized based on each patient’s ability and level of pain. Exercises were performed using series 1 to 3, with 8 to 15 repetitions, and isometric contractions lasting 5 to 10 seconds. There were 30-second breaks between series, and 2 to 3 minutes between exercises. The exercises performed during this phase are listed in Tables 6–8.

**Table 6 pone.0309935.t006:** Phase 2C exercises schedule for the first, third, fifth and seventh sessions.

	Sessions 1, 3, 5 and 7						
	Exercise	Series	Repetitions	Intensity	Duration	Break	Effort
**Block 1**	*Bracing + press pallof vertical a stride*	4	8–10	5/10	1,3,2	-	Low
	*Standing iso hold anti extensor*	3	8x5”	7/10	-	30”	Low
	*Standing hip extension iso push at 30° hip flexion with blocked core*	3	5x7”	9/10	-	-	High
**Block 2**	*Hip extension iso push standing in one leg in asymmetric ground + soft hinge with KB in goblet quad*	3	10	7/10	-	120”	Low
	*A stride ascending row for dorsal extension without blocked lumbar*	3	12–15	8/10	1,3,3	-	Moderate
	*Horizontal press pallof from knees*	3	12	7/10	1,3,2	-	Low
**Block 3**	*One hand from knees with the contrary foot raised*	3	8	8/10	1,2,3	-	Moderate
	*Hip extension in prone position*	3	20–25	8/10	1,3,3	-	Moderate
	*Isotonic clamshell*	3	20–25	8/10	-	120”	Moderate

**Table 7 pone.0309935.t007:** Phase 2C exercises schedule for the second, forth, sixth and eight sessions.

	Sessions 2, 4, 6 and 8						
	Exercises	Series	Repetitions	Intensity	Duration	Break	Effort
**Block 1**	*Iso switch dead bug changing support + iso hold anti extension arms + bracing*	3	10	8/10	-	30”	Moderate
	*A stride iso push in extension from arms and from below activating spinal extensors + creating speed peaks and contraction intensity*	4	10x7”	8/10	-	60”	Moderate
	*Bird dog*	3	10	5/10	-	-	Minimal
**Block 2**	*Iso push hip extension standing in one leg over asymmetric stand + iso switch KB changing hands*	3	15	8/10	-	-	Moderate
	*Dorsal Jefferson curl for dorsal with blocked lumbar*	3	8	6/10	-	-	Minimal
	*Post-isometric Koala*	3	10	6/10	-	120”	Minimal
**Block 3**	*Iso holds pelvic retroversion with elastic band standing in asymmetric stand + thoracic flexo-extension with KB in goblet squat*	3	15	7/10	-	-	Low
	*Monsters walk for medial gluteus guided in parallel*	3	15/side	8/10	-	-	Moderate
	*Iso bird dog + row + hip extension in a bench*	3	8/side	8/10	-	120”	Moderate

**Table 8 pone.0309935.t008:** Phase 2C exercise schedule for the home exercises.

	Home exercises						
	Exercise	Series	Repetitions	Intensity	Duration	Break	Effort
**Block 1**	*Clamshell with blocked lumbar*	3	20–25	8/10	-	-	Moderate
	*Standing iso push hip extension at 30° with blocked core*	3	5x7”	9/10	-	-	High
	*Step up with pre-iso push to 3” step*	3	6–8	7/10	-	120”	Low
**Block 2**	*Monsters walk for medial gluteus guided in parallel*	3	15/side	8/10	-	-	Moderate
	*Standing anti extensor iso hold*	3	8x5”	7/10	-	30”	Low
	*Standing horizontal press pallof in asymmetric stand + bracing*	3	12–15	8/10	1,3,3	-	Moderate

*Phase 3. Movement strategies*

Phase Three comprises day 90 onward. As per the existing guidelines at this time, the electrode ought to be firmly in place, with minimal probability of relocation. During this phase, the spinal flexion shall be 155 degrees, and the spinal extension shall be 115 degrees. The range of spinal movement shall be complete, enabling patients to incorporate movement into their daily routines. Concentric and eccentric contractions are likewise employed in everyday life. The exercises are listed in Tables 9–12.

**Table 9 pone.0309935.t009:** Phase 3 exercise schedule for the first, third and fifth sessions.

	Sessions 1,3 and 5						
	Exercise	Series	Repetitions	Intensity	Duration	Break	Effort
**Block 1**	*Horizontal press pallof from knight with soft core flexion*	3	5 x 3”	8-9/10	-	30”	Moderate
	*Standing iso push hip extension at 30° with blocked core*	3	5x7”	9/10	-	-	High
	*Iso push gluteal bridge + iso hold arms anti extensor + cervical- thoracic flexion facing up + hollowing*	3	5 x 3”	8-9/10	-	30”	Moderate
**Block 2**	*Iso push hip extension standing on leg over asymmetric stand + complete hinge and KB with briefcase hold*	3	10	7/10	2,2,1	120”	Low
	*Iso hold vertical press pallof + switching from symmetric to asymmetric stand*	3	5/side	6/10	-	-	Low
	*Thrust with block and KB in open side*	3	8/side	8/10	-	120”	Moderate
**Block 3**	*Dead weight from block + hip extension with elastic band + bracing*	3	8–12	8/10	1,1,3	-	Moderate
	*Iso push wall drill*	3	15/side	8/10	-	-	Moderate
	*Step hip thrust + bracing*	3	8–12	8/10	1,3,3	120”	Moderate

**Table 10 pone.0309935.t010:** Phase 3 exercise schedule for the second, fourth and sixth sessions.

	Sessions 1,3 and 5						
	Exercise	Series	Repetitions	Intensity	Duration	Break	Effort
**Block 1**	*Vertical press pallof from knight with soft core flexion*	3	5 x 3”	8-9/10	-	30”	Moderate
	*Iso push hip extension at 90° de flexion*, *standing with blocked core*	3	5x7”	9/10	-	-	High
	*Iso push gluteal bridge+ iso hold arms anti extensor + cervical- thoracic flexion facing up + hollowing*	3	5 x 3”	8-9/10	-	30”	Moderate
**Block 2**	*Hack squat + bracing*	3	10	7/10	2,2,1	120”	Low
	*Iso hold vertical press pallof + switching from symmetric to asymmetric ground*	3	5/side	6/10	-	-	Low
	*Pendlay row in asymmetric ground with KB*	3	10/side	8/10	1,2,3	60”	Moderate
**Block 3**	*Seal row with extended legs and blocked lumbar with a cushion*	3	10/side	8/10	1,2,3	-	Moderate
	*Dynamic dorsolumbar rotation from thrust*	3	15/side	8/10	-	-	Moderate
	*Lead carries for pelvic stability*	3	10 steps/side	6/10	-	120”	Low

**Table 11 pone.0309935.t011:** Phase 3 exercise schedule home exercises A.

	Home exercises A						
	Exercise	Series	Repetitions	Intensity	Duration	Break	Effort
**Block 1**	*Clamshell with blocked lumbar*	3	20–25	8/10	-	-	Moderate
	*Ascending row with dorsal rotation over*	3	5x7”	9/10	-	-	High
	*Post isometric koala*	3	6–8	7/10	-	120”	Low
**Block 2**	*Monster walk for medial gluteus guided in parallel*	3	15/side	8/10	-	-	Moderate
	*Iso push hip internal rotation and flexion from dead bug + forced exhalation*	4	5x5”	9/10	-	-	High
	*Iso push hip extension standing in one leg over asymmetric ground + complete hinge and KB with briefcase hold*	3	10	7/10	2,2,1	120”	Low

**Table 12 pone.0309935.t012:** Phase 3 exercise schedule for home exercises B.

	Home exercises B						
	Exercise	Series	Repetitions	Intensity	Duration	Break	Effort
**Block 1**	*Prone lumbar extension*	3	20–25	8/10	-	-	Moderate
	*Jefferson curl without weight*	3	5x7”	9/10	-	-	High
	*Post isometric koala*	3	6–8	7/10	-	120”	Low
**Block 2**	*Dorsolumbar inclination with elastic band*	3	15/side	8/10	-	-	Moderate
	*Iso push internal rotation and hip flexion from dead bug + force exhalation*	4	5x5”	9/10	-	-	High
	*Hip abduction sitting on the floor with fixed back*	3	10	7/10	2,2,1	120”	Low

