The application of integrated interventions may lead to enhanced results in both the short-term and medium-term periods [28]. Combining SCS therapy with physical exercise may not only improve outcomes, but it may also result in a higher number of patients experiencing sustained benefits. However, it is important to consider the potential adverse events that may occur when implementing spinal cord stimulation (SCS) and exercise together, such as electrode migration. Approximately one in ten patients who receive SCS implants experience lead migration [29]. Additionally, the high incidence of lead displacements (3.07%) should not be overlooked [30]. According to the postoperative treatment guidelines, patients are advised to refrain from engaging in any form of exercise or assuming positions that involve the end range of motion in the lumbar spine for a period of two months following the operation. This precautionary measure is necessary as it can potentially result in the migration of the implanted electrode. It is essential to allow sufficient time for the surrounding tissues to undergo fibrosis and securely anchor the electrode in place. Patients with PSPS T2 may have protective attitudes influenced by fear of pain due to movement (kinesiophobia), which can exacerbate patient deconditioning [31]. Therefore, treatment should focus on enhancing the patient’s perceptions and beliefs about movement and addressing not only mechanical and functional parameters but also improving the overall experience [32]. The use of both treatment techniques (SCS/exercise) has resulted in moderate-quality evidence, presenting low-effect measurements when applied in isolation [33]. Furthermore, implementing an exercise protocol that minimizes the risk of adverse effects is crucial. Designing an exercise program based on the range of motion of the spine may be particularly beneficial in avoiding adverse effects on SCS. This study aimed to evaluate the effect of combined treatment with SCS and exercise focused on neuromuscular control of CORE in comparison with isolated treatment with SCS on functionality, pain perception, psychosocial variables, patient satisfaction, adverse effects, and quality of life in patients diagnosed with PSPS-T2. Based on these recommendations, the hypothesis proposed in this study aimed to capitalize on the analgesic effect of posterior cord stimulation during a window of opportunity while the patient underwent re-education through neuromuscular and core control exercises. The integration of these two treatment techniques is expected to yield superior effects compared to the application of a single treatment in isolation.

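### The stated 24 exercise sessions do not follow from two a week for eight weeks, and the phase schedule fits neither an eight-week programme nor 16 sessions

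*Protocol article*

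**What the plan says.** The protocol article describes the exercise programme in three ways.

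- **Abstract, Methods/Materials:** "Two sessions per week will be scheduled for 8 weeks with a total of 16 sessions".
- **Section 4.1.1, opening paragraph:** "Two weekly sessions, each lasting 60 minutes and spanning eight weeks, will constitute a total of 24 sessions".
- **Section 4.1.1, phases:** Phase 1: "This phase will last for 15 days, comprising of four sessions". Phase 2A: "The second phase of treatment will span from day 16 to day 37 after the intervention", with six monitored sessions. Phase 2B covers days 38 to 60, with no session count and no table of its own. Phase 2C: "Phase 2C encompassed the period from days 61 to 90 following the intervention", with eight sessions in Tables 6 and 7. Last, "Phase Three comprises day 90 onward", with six sessions in Tables 9 and 10 and no end date.

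On exercise type, the Phase 2C text says: "To ensure proper exercise adherence, all exercises were performed isometrically". Table 6, which belongs to that phase, lists an isotonic clamshell.

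On timing, the Background reports postoperative guidance under which "patients are advised to refrain from engaging in any form of exercise or assuming positions that involve the end range of motion" of the lumbar spine for two months after the operation. Section 2.5 introduces the exercise programme after surgery without naming a day. The phases count days from the intervention, a term that section 4.1.1 does not define.

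**The concern.** The first two statements use the same frequency and the same duration and reach different totals, so at least one of them is wrong as printed. The phase schedule is a third version and agrees with neither on length.

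Three things depend on the answer. Section 8.2.2 plans a per-protocol analysis, which needs one programme against which a participant counts as compliant. Section 6 expects the exercise group to perform the exercises with the instructed regularity, and that regularity has no single source. Section 2.5 schedules a measurement at two months. Under an eight-week programme this is an end-of-treatment measurement; under the phases, treatment is still going on.

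The relation between the phase calendar and the two-month advice also bears on recently implanted patients, and the text leaves it open.

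**Working it through.** **1. The stated total.** Inputs from section 4.1.1: 2 sessions a week, 8 weeks. 2 × 8 = 16, so the stated 24 is not reproduced. It is 24/16 = 1.5 times what its inputs give, or 24 × 60 = 1,440 minutes against 16 × 60 = 960. Reaching 24 would take 24/2 = 12 weeks at two a week, or 24/8 = 3 a week over eight weeks. The Abstract's 16 does follow from the same inputs.

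**2. The phase calendar.** Days are counted inclusively.

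| Phase | Days | Length | Sessions printed | Sessions per week |
|---|---|---|---|---|
| 1 | 1–15 | 15 | 4 | 4/15 × 7 = 1.87 |
| 2A | 16–37 | 22 | 6 | 6/22 × 7 = 1.91 |
| 2B | 38–60 | 23 | none | – |
| 2C | 61–90 | 30 | 8 | 8/30 × 7 = 1.87 |
| 3 | 90 onward | open | 6 | – |

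The Phase 3 count follows the table captions. The column header of Table 10 repeats the session numbers of Table 9.

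- Length: eight weeks is 56 days. Day 90 is 90/7 = 12.9 weeks, and 90/56 = 1.6 times as long, before Phase 3. Six Phase 3 sessions at two a week would add three weeks, to about day 111.
- Sessions as printed: 4 + 6 + 8 + 6 = 24, with nothing counted for Phase 2B.
- Sessions if Phase 2B also has six: 4 + 6 + 6 + 8 + 6 = 30. This is an assumption, based on the statement that 2B shares the aims and features of the preceding phase. The running total is then 16 by day 60, 24 by day 90 and 30 with Phase 3.
- The rate stays near two a week wherever it can be computed. The conflict therefore lies in the duration and the total, not in the frequency.
- Day 90 belongs to both Phase 2C and Phase 3.

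**3. Text against table.** The Phase 2C text allows only isometric work. Table 6 contains an exercise named as isotonic. Both cannot stand.

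**4. Day 1 and the two-month advice.** Section 2.5 places the exercise after surgery, and the Phase 3 text links day 90 to the electrode being fixed. Both point to implantation as day 1, but neither says so. On that reading Phases 1, 2A and 2B occupy days 1 to 60, which is essentially the whole two-month period named in the Background.

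**5. The two-month visit.** This step assumes that visits and phases share one origin. Two months is about day 60. That is just after day 56, the end of an eight-week programme, but it is the end of Phase 2B in the phase calendar, with 2C and 3 still to come.

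**The case against.** The fairest defence is that the three versions may be reconcilable. With six sessions in Phase 2B, 16 is the count to day 60 and 24 the count to day 90, so the two totals may describe different stretches of one programme. That is plausible, but the document does not say it. It attaches both totals to eight weeks, and 24 is equally the sum of the printed counts with Phase 2B left out. Nor can the later phases be set aside as home exercise: Tables 6, 7, 9 and 10 list numbered sessions apart from the home schedules in Tables 8, 11 and 12.

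A second defence concerns timing, and much of it stands. The Background describes general guidance, and its wording can be read as barring all exercise or only exercise at end range. The same section proposes a programme built on spinal range of motion in order to protect the electrode, and section 4.1.1 sets flexion and extension limits by phase. A reader might infer that the trial plainly starts exercise inside a restriction and leaves lead-migration risk undefined. The documents do not support that. The overlap depends on day 1 being implantation and on how the guidance is read, and the protocol does limit movement. What it lacks is a statement of how those limits answer the advice.

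A reader might also infer a near two-fold difference in treatment. The stated totals differ 1.5-fold, and eight weeks against day 90 is 1.6-fold. Only the assumed 30 sessions approach two-fold (30/16 = 1.9). The migration rates quoted in the Background describe recipients of spinal cord stimulation in general and add nothing to a point about schedule.

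**Conclusion.** The point holds and must be fixed. Without any assumption, the total of 24 contradicts its own inputs and the Abstract, the phases run well past eight weeks with no end, Phase 2B has no session count, day 90 is in two phases, and the Phase 2C text conflicts with Table 6. The programme is thus 16 or 24 sessions as stated, or 30 on the assumption that Phase 2B has six, over eight weeks, about 13 weeks or an open period.

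The overlap with the two-month advice is conditional. It rests on day 1 being implantation and on the wider reading of the guidance. What is unconditional is that the protocol neither defines day 1 nor relates its movement limits to the advice.

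The statistical consequence is that the per-protocol set and adherence lack a single reference, and the two-month result cannot be labelled as on-treatment or end-of-treatment. These are conflicts between printed statements, so they are not detail that an article may leave to a fuller document.

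**What to change.** By amendment, reconcile the Abstract, the Background, section 2.5 and section 4.1.1 with its tables, so that they give:

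- one session total, with a count for Phase 2B;
- one programme duration with a stated end, and day 90 in one phase only;
- one definition of day 1, tied to a named event;
- an explicit statement of how the schedule and its range-of-motion limits relate to the cited two-month advice;
- Phase 2C text that matches its tables.

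Which version is right is for the clinical team to decide. Then use the reconciled programme as the reference for adherence and for the per-protocol set in section 8.2.2, and state whether the two-month visit falls during or after treatment.

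The cost is a protocol amendment with clinical sign-off. It needs no new visits, procedures or data.
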